### Statistical Analyses

Power analysis for the matched-pair *t* test was conducted. With the lower limit of the medium effect size of 0.5 [37], sample sizes of 27 and 36 provided 80% and 90% power, respectively, under 1-sided directional null hypothesis and the nominal significance rate of .05. We will aim to enroll 30 participants for this feasibility and fidelity study.

Once data are clean, descriptive statistics will be computed and examined. For the primary outcome, benefit will be determined by an increase in responsive feeding codes pre-post SS-OO-PP-RR coaching sessions (visits 2 and 5). IFQ subscale scores will be analyzed using matched sample *t* tests for pre-post coaching sessions to determine the benefit of the intervention. If the assumptions of statistical tests are not clearly met, the Mann-Whitney *U* test would be considered as an alternative. In a future pilot randomized controlled trial (RCT), analysis of covariance (ANCOVA) will be conducted where the difference between treatment and control groups for the postmeasure is examined with the premeasure as a covariate. The use of ANCOVA provides a statistical control in addition to the design control for the premeasure via random assignment in the RCT.

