### Setting and Participants

Mothers of any parity will be recruited from community settings during the third trimester (28 weeks and beyond) of a healthy pregnancy. To be eligible, mothers need to be aged 18 years or older, able to read and speak English, and agree to video recording of an infant feeding in their home. Any medical or congenital condition in the fetus that would interfere with infant feeding or growth (ie, Down syndrome or cleft lip or palate) will be excluded. Mothers will be enrolled in the third trimester and then screened again after the birth of the infant to ensure that mother and infant remain eligible to participate.

An interventionist will be recruited to deliver the LEIFc intervention in the homes of new mothers. He or she will ideally have a background in maternal-child health and may be a nurse, social worker, speech-language pathologist, dietician, or early child development specialist. The interventionist will be trained on the SS-OO-PP-RR approach and the LEIFc protocol. Because the purpose of this study is to test the fidelity and feasibility of the intervention, feedback from the interventionist will be sought as part of the research protocol.

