### Outcome Measures

The primary outcome in this study is the use of responsive feeding. This will be measured before (study visit 2) and after (study visit 5) intervention. Data are obtained subjectively through evaluation of the IFQ and objectively through a video review. The IFQ will provide a subjective measure of responsive feeding. This 20-item self-report tool has been validated for use in mothers of infants [29,34,35]. Likert-type scoring is used; higher scores indicate a stronger measure of the construct. Three subscales will be used to measure responsive feeding: use of food to calm, use of food to soothe, and awareness of infant cues.

The objective measure of responsive feeding will be collected via coding of the video session before and after intervention. The research team developed a coding scheme to capture both mother and infant behaviors during the feeding interactions. The coding scheme was adapted from the Responsiveness to Child Feeding Cues Scale [36] to define specific, discrete maternal behaviors that relate to responding to infant hunger and satiety cues as well as early infant communication acts. Infant behaviors are coded for hunger, satiety, and early communication acts. Research assistants will be trained on the coding scheme and will use existing videos to code with a goal of at least 85% agreement achieved to confirm inter-rater reliability. The coding scheme developed by the team will be used to code the feeding interactions for study visits 2 and 5. Videos will be coded for the number and rate of maternal utterances directed toward the child and responsiveness to the child’s vocalizations using the Noldus Observer XT software. The percentage of the interactions spent jointly engaged between the mother and the infant will also be coded.

Infant feeding practices, demographic characteristics (ie, maternal age, marital status, education level, and race and ethnicity), and maternal depression will be considered as covariates. Initiation and duration of breastfeeding and age at complementary food introduction will be extracted from data and tabulated into variables: duration of breastfeeding (any and exclusive) calculated in weeks and age at complementary food introduction calculated in weeks. Demographic data are collected at study visit 1, infant feeding practices at study visits 2 through 5, and maternal depression (via the Patient Health Questionnaire-9) at study visits 2 through 5.

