## Discussion

### Anticipated Findings

Although data collection for this study is ongoing, it is anticipated that the LEIFc intervention will be feasible to implement with and socially acceptable to mother-infant dyads by a trained interventionist. Additionally, it is hypothesized that fidelity of the intervention would need to be refined to better meet the needs of mother-infant dyads, especially those from high-risk populations (ie, minority groups and low socioeconomic status). Qualitative data collected from mothers (visit 5) and from the interventionist (visits 3 and 4) will be used to refine the intervention. Finally, it is hypothesized that there may be a change in responsive feeding before or after intervention; however, it cannot be attributed to the intervention until tested with a control group, in the future planned RCT.

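### The sample sizes are right for one 1-sided paired t test, but benefit on the primary outcome is judged on at least four measures with no hierarchy or multiplicity rule

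*Protocol article*

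**What the plan says.** **Sample size.** In the Statistical Analyses section the article reports: "Power analysis for the matched-pair *t* test was conducted". The inputs are "With the lower limit of the medium effect size of 0.5", "under 1-sided directional null hypothesis and the nominal significance rate of .05". The result is that "sample sizes of 27 and 36 provided 80% and 90% power, respectively". The target follows: "We will aim to enroll 30 participants for this feasibility and fidelity study".

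**Primary outcome.** Outcome Measures names one primary construct, the use of responsive feeding, compared between study visits 2 and 5. It has two sources: "Data are obtained subjectively through evaluation of the IFQ and objectively through a video review". Three IFQ subscales are assigned to the construct. The video is scored with a team-built coding scheme for maternal and infant behaviors.

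**Decision on benefit.** Statistical Analyses ties benefit on the primary outcome to an increase in the responsive feeding codes, in the plural and without naming a code or summary score. It then says that matched t tests on the IFQ subscales will also determine benefit. The Abstract, after describing both the survey and the video measures, says that responsive feeding before and after the intervention will be analyzed by matched t tests. No hierarchy, combination rule or adjustment is given.

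**The concern.** A power statement describes a decision only if the decision rests on the test that was powered. Here one test was powered, at one .05, while at least four results can each be read as showing benefit. The article does not say whether one positive result is enough, whether all must be positive, or whether the video codes come first.

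The stake is how a positive pre-post result is read when the intervention is refined and moved to the next ORBIT phase. With several measures and no declared order, the measure that happens to move can become the evidence of benefit, and the published .05 and 80% would not describe that decision.

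**Working it through.** **Inputs from Statistical Analyses:** matched-pair t test; effect size 0.5, read as the mean of the paired differences divided by their standard deviation; 1-sided .05; n = 27 and 36; enrolment 30.

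**Inputs from Outcome Measures and Statistical Analyses:** three IFQ subscales plus at least one video-code measure, so at least 3 + 1 = 4.

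**Assumed, because the article gives no figure:** the correlation between the four measures, varied from 0 to 0.9.

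**Step 1: reproduce the stated sizes.** Power is the probability that a noncentral t variable with n − 1 degrees of freedom and noncentrality 0.5 × √n exceeds the 1-sided .05 critical value.

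| Complete pairs | Noncentrality | Power, one test at .05 |
|---|---|---|
| 26 | 0.5 × √26 = 2.55 | 79.8% |
| 27 | 0.5 × √27 = 2.60 | 81.2% |
| 30 | 0.5 × √30 = 2.74 | 84.8% |
| 35 | 0.5 × √35 = 2.96 | 89.5% |
| 36 | 0.5 × √36 = 3.00 | 90.3% |

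The smallest n reaching 80% is 27, and the smallest reaching 90% is 36. The stated figures are correct. They count pairs, that is, dyads with both a visit 2 and a visit 5 measurement.

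**Step 2: error rate if any one of four counts.** With independent measures the chance of at least one false positive is 1 − 0.95⁴ = 1 − 0.8145 = 0.185. For correlated measures it was simulated (40,000 replicates, equal correlation, n = 27 and n = 30, which agree to within half a percentage point):

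| Assumed correlation | Chance of at least one false benefit |
|---|---|
| 0 | about 19% (exact 18.5%) |
| 0.3 | about 16% |
| 0.5 | about 15% |
| 0.7 | about 12% |
| 0.9 | about 9% |

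That is roughly two to four times the nominal 5%.

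**Step 3: power if the error rate is protected.** Bonferroni over four gives 0.05 / 4 = 0.0125 per test. Power per measure is then 59.1% at 27 pairs and 64.7% at 30, and 41 complete pairs would be needed for 80%.

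**Step 4: power if all four must succeed.** Under independence, joint power is 0.812⁴ = 43% at 27 pairs and 0.848⁴ = 52% at 30. Positive correlation would raise these figures.

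**Step 5: what 30 enrolled allows.** 30 − 27 = 3 dyads, and 3/30 = 10%. Thirty enrolled therefore yields the 27 pairs if no more than three dyads are lost between prenatal enrolment and visit 5.

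The stated power and the stated .05 hold together in only one case: a single named variable carries the test.

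**The case against.** **There is no arithmetic error, and .05 is called nominal.** Both are true. The article makes no explicit family-wise claim, and it states no rule that any one success is enough, so the 9% to 19% is conditional on that rule. But the article does let both the codes and the IFQ tests decide benefit without saying how they combine, and no available rule gives both stated figures across four measures.

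**The video codes are already primary.** The analysis section does link the primary outcome most closely to the codes. They remain a set and not one variable, and Outcome Measures places the IFQ under the same primary outcome.

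**This is an uncontrolled feasibility study.** It is, and the Discussion says that a change cannot be attributed to the intervention without a control group. That lowers the consequence. It does not address chance findings, and the article still publishes a power figure and a benefit rule that should match.

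A reader might infer more than the document supports:

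- *That power will fall below 80% because mothers enrol before birth and dyads are* "screened again after the birth of the infant to ensure that mother and infant remain eligible". The article gives no loss rate. A shortfall needs an assumed loss above 10%, and at an assumed 20% (24 pairs) power is still 76.8%.
- *That the two earlier participants without successful data collection indicate attrition.* They belong to the 2020 attempt, which used videoconferencing. Visits 2 to 5 now take place in the family home.
- *That the Discussion contradicts the 1-sided test by saying* "it is hypothesized that there may be a change in responsive feeding before or after intervention". This is a caveat about attribution, not a test specification. The analysis section defines benefit as an increase, which fits a 1-sided test.
- *That the utterance, vocal-responsiveness and joint-engagement codings add further tests of benefit.* No benefit rule is stated for them by name, and the Introduction calls communication a secondary focus.

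**Conclusion.** The concern holds as a mismatch between the powered test and the decision on benefit. The sizes 27 and 36 are correct for one 1-sided paired t test. Benefit is judged on at least four measures with no hierarchy or multiplicity rule.

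If one success suffices, the chance of a false benefit is about 9% to 19%, assuming exactly four tests and an equal correlation between 0.9 and 0. If the error is controlled by Bonferroni, power per measure is 59% to 65% for 27 to 30 pairs.

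These are alternatives. Unadjusted, each test keeps at least 80% power with 27 or more pairs and only the overall error rate is lost; adjusted, the error rate is kept and power is lost. A reader might conclude that both fail together, but that does not follow. The point deserves correction because the remedy is cheap; it does not undermine the feasibility and fidelity aims.

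**What to change.** In Statistical Analyses:

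1. Name one quantitative video-coded responsive-feeding measure, with its definition, and make its change from visit 2 to visit 5 the single tested primary variable. State that the power calculation refers to this test. Make the choice before the coded visit 2 and visit 5 data are compared.
2. Report the three IFQ subscales and all other codes descriptively, as mean changes with 95% confidence intervals, and remove the statement that the IFQ tests determine benefit. Align the Abstract and Outcome Measures with this.
3. State that 27 and 36 are completed visit 2 to visit 5 pairs, and that 30 enrolled therefore allows for the loss of 3 dyads (10%).

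The target of 30 and the 1-sided .05 stay as they are. The cost is a wording change and one real concession: the IFQ subscales no longer decide benefit. If the team wants to keep them in that role, the alternative is to state a multiplicity rule and its power. With Bonferroni over four that is 65% per measure at 30 pairs, or 41 pairs for 80%.

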### Study Design and Intervention

This study uses a pre-post quasi-experimental design with no control group to examine the feasibility, fidelity, and social validity of the LEIFc intervention. The intervention was developed based on existing literature regarding enablers and barriers to the use of responsive feeding by caregivers and communication cues present early in life. The multicomponent LEIFc intervention involves maternal education on responsive feeding practices and mother-infant communication while using a family-guided caregiver coaching approach called SS-OO-PP-RR (“super,” Setting the Stage, Observation and Opportunities, Problem Solving and Planning, Reflection and Review) during feeding sessions [31,32]. The SS-OO-PP-RR approach was developed based on adult learning theory and has been successfully used with parents and childcare providers to promote development across domains in infants and young children [31-33]. For the LEIFc intervention, SS-OO-PP-RR was modified to be specific to communication during feeding to promote responsive feeding (Textbox 2). It is used as a guide for the interventionist during the coaching session but will also be used to evaluate the fidelity of the intervention. The objective measure of responsive feeding will occur through video recording of feeding sessions between mothers and infants. Videos will be coded before the intervention and then after 2 coaching sessions between the interventionist and the mother during a feeding session. The subjective measure of responsive feeding will be collected via a self-report questionnaire completed by mothers before and after the intervention study visits.

The “super,” Setting the Stage, Observation and Opportunities, Problem Solving and Planning, Reflection and Review intervention.

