### Procedures

Eligible mothers will be identified through community settings such as obstetrician offices, prenatal parenting or birth classes, social media forums that pregnant moms may frequent, and word of mouth. If eligible and interested in the study, study personnel will consent mothers for the study. Once enrolled in the study, the interventionist will implement each study visit (Table 1). Study visit 1 is conducted when the mother is in the third trimester of pregnancy. Written material on infant feeding and infant cues of hunger and satiety is provided. Additionally, 2 short videos, one on infant hunger cues and the second on infant satiety cues, are watched with the interventionist and the mother. Any questions on feeding or communication are answered by the interventionist. Study visit 2 is conducted when the infant is approximately 1 month old. At this visit, a video recording of a feeding session between the mother and the infant is taken with no interaction with the interventionist. The feeding can be from the breast or from the bottle (with breastmilk or formula). Study visits 3 (at infant age of 2 months) and 4 (at infant age of 3 months) are the intervention study visits. At each visit, the interventionist will use the SS-OO-PP-RR tool to coach the mother through the feeding to identify hunger and satiety cues and discuss ways to respond. Each of these visits is also video recorded. The final study visit is at infant age of 4 months when another video recording of the infant feeding session is taken with no coaching from the interventionist.

At study visit 1, demographic data are collected along with the mother’s prenatal plans for infant feeding. At study visit 2, birth history is collected along with infant feeding practices, and the mother completes the Infant Feeding Questionnaire (IFQ). During study visits 3 and 4, infant feeding practices are collected. At study visit 5, the mother completes the IFQ and provides feedback on the study itself through a series of qualitative questions.

**Table 1 table1:** Timing of study visits and procedures.

Study visit	Timing of visit	Components of the visit	Visit location
1	Prenatal (28 weeks or beyond of gestation)	Education provided on communication with your baby during feeding—videos and written material	Video conferencing platform (Zoom)

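### The paired visit 2 to visit 5 tests are said to determine the intervention's benefit, which a single-group contrast cannot do and which the Discussion disclaims; visit 2 is also pre-coaching, not pre-intervention

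*Protocol article*

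**What the plan says.** **Rule for benefit.** Statistical Analyses judges the primary outcome in two ways. Benefit is read from an increase in responsive-feeding video codes between visits 2 and 5, and the IFQ subscales are compared by matched t tests over the same two visits "to determine the benefit of the intervention".

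**Attribution.** In the Discussion, Anticipated Findings expects that responsive feeding may change, then adds: "however, it cannot be attributed to the intervention until tested with a control group".

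**Design.** Study Design and Intervention states: "This study uses a pre-post quasi-experimental design with no control group".

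**What the intervention is.** The same section says: "The multicomponent LEIFc intervention involves maternal education on responsive feeding practices and mother-infant communication", combined with the coaching approach.

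**When the components are given.** Under Procedures, at the prenatal visit 1, "Written material on infant feeding and infant cues of hunger and satiety is provided", and "2 short videos, one on infant hunger cues and the second on infant satiety cues, are watched with the interventionist and the mother". Then: "Study visit 2 is conducted when the infant is approximately 1 month old". Coaching takes place at visits 3 and 4 (2 and 3 months), and visit 5 is at 4 months. Procedures applies the term intervention visits to visits 3 and 4 only.

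**How the baseline is labelled.** Outcome Measures says of the primary outcome: "This will be measured before (study visit 2) and after (study visit 5) intervention". The Methods paragraph of the Abstract uses the same labels.

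**The concern.** There are two faults, and both affect what the trial may conclude.

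First, to determine the benefit of an intervention is to attribute a change to it. The Methods text sets that as the decision rule for the primary outcome, and the Discussion says the attribution cannot be made. An analyst works from the Methods. As that section stands, a significant paired test is to be reported as benefit, although the same result would follow from mothers gaining experience and infants growing from 1 to 4 months with no coaching at all.

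Second, the term intervention covers the whole programme in one section and coaching alone in others. Under the whole-programme definition, visit 2 is not before the intervention, because the education has already been given. A reader who combines that definition with the before/after labels would take the contrast as the effect of education plus coaching. It contains no education effect acquired before visit 2.

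**Working it through.** **1. Order of events, from Procedures and Table 1**

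| Visit | Timing | Programme component | Primary outcome measured |
|---|---|---|---|
| 1 | prenatal | education (written material, videos) | no |
| 2 | about 1 month | none | IFQ and video |
| 3 | about 2 months | coaching | no (filmed, but only visits 2 and 5 are coded for the outcome) |
| 4 | about 3 months | coaching | no (as visit 3) |
| 5 | about 4 months | none | IFQ and video |

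The interval between the two outcome measurements is 4 − 1 = 3 months. The mean change over it is

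change(2→5) = coaching effect + natural change over 3 months.

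There is one group and there are two measurement times, so the two terms cannot be separated. Adjusting for the covariates listed in Outcome Measures does not help, because every infant ages by about the same three months. An education effect already present at visit 2 enters both measurements and cancels from the difference.

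**2. The plan's own power figures**

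Inputs from Statistical Analyses: standardised paired difference d = 0.5, one-sided α = .05, n = 27 and 36, planned enrolment 30.

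Formula: power = P(T > t(0.95; n−1)), where T is noncentral t with n−1 degrees of freedom and noncentrality d√n.

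- n = 27: noncentrality 0.5 × √27 = 2.598; power 81.2%.
- n = 36: noncentrality 0.5 × √36 = 3.000; power 90.3%.
- n = 30: noncentrality 0.5 × √30 = 2.739; power 84.8%.

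The smallest n reaching 80% and 90% are exactly 27 and 36, so the stated figures reproduce. No number in the plan is disputed.

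**3. Illustration: natural change read as benefit**

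The same formula applies with n = 30 complete pairs, a coaching effect of zero, and d replaced by an assumed natural drift in units of the SD of the paired difference. The document gives neither the size nor the direction of any drift. Figures are for one measure.

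| Assumed drift (SD) | Noncentrality | Probability of a significant result |
|---|---|---|
| −0.2 | −1.095 | 0.3% |
| 0 | 0 | 5% |
| 0.1 | 0.548 | 13% |
| 0.2 | 1.095 | 28% |
| 0.3 | 1.643 | 48% |
| 0.5 | 2.739 | 85% |

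The test's null hypothesis is zero mean change. With real drift that null is false, so these rejections are correct detections of change. They become false conclusions only when reported as benefit of the intervention.

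**4. Illustration: education effect excluded**

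Suppose, again as an assumption, that the whole programme is worth 0.5 SD with no drift, and that education has produced 25%, 50% or 75% of it before visit 2. The contrast then contains 0.375, 0.25 or 0.125 SD, and power at n = 30 falls from 85% to 64%, 38% or 17%. Read as the effect of the whole programme, the change would be too small.

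**The case against.** The best defence is that the document is open about its design. It declares a single group in the Abstract and in the Methods, and Theoretical Framework places the study in phase I of the ORBIT model, where an uncontrolled feasibility study is acceptable. Statistical Analyses describes the contrast as before and after coaching in both sentences at issue. The order of education, baseline and coaching is set out plainly. Education is prenatal and no feed can be filmed before birth, so a video baseline before education is impossible. All of this stands. It narrows the point to the benefit rule and the labels; it does not remove the conflict between the Methods and the Discussion.

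A reader might infer more than the document supports:

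- *That the Discussion concedes the maturation and education problems.* It concedes only that there is no control group. The other two follow from the visit schedule.
- *That visit 2 is an invalid baseline.* It is valid for coaching. It is wrong only as a baseline for the programme as Study Design and Intervention defines it.
- *That the observed change will be carried into the later randomised trial.* No section says so. The Conclusions speak of refining the intervention and moving to the next phase, and Statistical Analyses mentions only that trial's ANCOVA.
- *That 28%, 48% and 85% are the test's type I error.* They rest on assumed favourable drifts and 30 complete pairs, and the test remains valid for mean change.
- *That an extra IFQ at visit 3, before coaching, would solve the problem.* It would say nothing about the video codes. It would set a one-month interval (visits 2 to 3) beside a two-month one (visits 3 to 5). Results also reports data collection as already under way.

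**Conclusion.** The point holds as a fault in the stated inference and the labels, not in the choice of design. Statistical Analyses gives the primary outcome a rule for declaring benefit that an uncontrolled contrast cannot support and that Anticipated Findings contradicts. Separately, visit 2 follows one component of the intervention as the document defines it, so the visit 2 to visit 5 change describes the coaching period only.

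Both faults can be read directly from the text and need no assumption. Their numerical size does need one. With assumed favourable drift of 0.2 to 0.5 SD, no coaching effect and 30 complete pairs, a result that the plan would call benefit occurs in 28% to 85% of trials. With zero drift it is 5%, and with unfavourable drift lower still. The document gives no basis for choosing among these. The wording should be corrected before the analysis, because it determines what the trial may claim.

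**What to change.** 1. In the Abstract (Methods), Outcome Measures and Statistical Analyses, label visit 2 as *post-education, pre-coaching* in place of before intervention.
2. In Statistical Analyses, replace both benefit statements, the one on video codes and the one on IFQ subscales, with: *estimate the mean change from visit 2 to visit 5 over the coaching period, with 95% CI; this is not an estimate of intervention benefit*. This brings the section into line with Anticipated Findings.

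The cost is wording only. No visit, measurement, participant or sample-size figure changes, and the data already being collected are sufficient. The price is that the trial gives up a claim of benefit, which its Discussion already says it cannot make.

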**Methods:**

This pre-post quasi-experimental study with no control group will recruit mothers (N=30) in their third trimester (28 weeks and beyond) of pregnancy from community settings. Study visit 1 will occur prenatally in which written and video material on infant feeding and infant hunger and satiety cues is provided. Demographic information and plans for infant feeding are also collected prenatally via self-report surveys. The use of responsive infant feeding via subjective (survey) and objective (video) measures is recorded before (study visit 2, 1 month post partum) and after (study visit 5, 4 months post partum) intervention. Coaching on responsive infant feeding during a feeding session is provided by a trained interventionist using the SS-OO-PP-RR approach at study visits 3 (2 months post partum) and 4 (3 months post partum). Infant feeding practices are recorded via survey, and infant weight and length are measured at each postpartum study visit. Qualitative data on the LEIFc intervention are provided by the interventionist and mother. Infant feeding videos will be coded and tabulated for instances of infant cues and maternal responses. Subjective measures of responsive infant feeding will also be tabulated. The use of responsive infant feeding pre-post intervention will be analyzed using matched *t* tests. Qualitative data will be examined to guide intervention refinement.

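### The only fallback named for the paired visit 2 versus visit 5 comparison is the Mann-Whitney U test, an independent-samples test with the wrong null variance when pre and post scores are correlated

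*Protocol article*

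**What the plan says.** All references are to the protocol article.

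- **Study Design and Intervention**: "This study uses a pre-post quasi-experimental design with no control group". There is one group of dyads.
- **Outcome Measures**, on the primary outcome (use of responsive feeding): "This will be measured before (study visit 2) and after (study visit 5) intervention". Table 1 has the same dyads complete the questionnaire and be filmed at both visits.
- **Abstract, Methods**: "The use of responsive infant feeding pre-post intervention will be analyzed using matched" *t* tests.
- **Statistical Analyses**, sample size: "Power analysis for the matched-pair" *t* test was done. "With the lower limit of the medium effect size of 0.5", one-sided at .05, "sample sizes of 27 and 36 provided 80% and 90% power, respectively". The target is 30.
- **Statistical Analyses**, test: "IFQ subscale scores will be analyzed using matched sample" *t* tests. The next sentence gives the fallback: "If the assumptions of statistical tests are not clearly met, the Mann-Whitney" U test would be considered.

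No paired rank test is named anywhere. The only two-group comparison mentioned is the ANCOVA for a future randomised trial, which has its own method.

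**The concern.** The design, the power analysis and the main test are all paired, but the fallback is not. Applied here, Mann-Whitney would treat 30 pairs as 60 independent observations. Its reference distribution assumes that the visit 2 and visit 5 scores are unrelated, whereas two measurements on the same mother usually are related.

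If the fallback were used, the p-value for the primary outcome would be miscalibrated. With positive correlation, a real pre-post change could be reported as no change, and the efficiency for which the sample size was chosen would be partly lost. This is not a detail left to a later document: the article names a specific test, and that test does not fit the design it describes.

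**Working it through.** **1. The article's own figures.** For a paired t test with n pairs and standardised mean difference 0.5 (SD of the differences), one-sided .05, power is P(T > t(0.95; n−1)), with T noncentral t on n−1 df and noncentrality 0.5√n.

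| n | Power |
|---|---|
| 26 | 79.8% |
| 27 | 81.2% |
| 30 | 84.8% |
| 35 | 89.5% |
| 36 | 90.3% |

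The smallest n for 80% and 90% are 27 and 36, as stated. The planned test is sound, and 0.5 behaves as an effect on the paired-difference scale.

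**2. Why the null variance is wrong.** Mann-Whitney assumes Var(U) = n²(2n+1)/12. On paired data with no change, the large-sample variance of U is that quantity times (1 − ρs), where ρs is the rank (Spearman) correlation between pre and post scores. For bivariate normal scores with correlation r, ρs = (6/π)·arcsin(r/2). The actual one-sided error is therefore about 1 − Φ(1.645/√(1 − ρs)).

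| r | ρs | √(1 − ρs) | 1.645/√(1 − ρs) | Actual error, formula | Actual error, simulated (n=30) |
|---|---|---|---|---|---|
| −0.2 | −0.191 | 1.091 | 1.507 | 6.6% | 6.4% |
| 0 | 0 | 1.000 | 1.645 | 5.0% | 5.1% |
| 0.3 | 0.288 | 0.844 | 1.949 | 2.6% | 2.4% |
| 0.5 | 0.483 | 0.719 | 2.287 | 1.1% | 1.2% |
| 0.7 | 0.683 | 0.563 | 2.921 | 0.2% | 0.2% |

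The nominal level is 5%. The signed-rank and paired t tests simulated at 4.7–5.2% across these correlations.

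**3. Power.** The simulation used 20,000 trials per setting, n = 30, bivariate normal scores with equal variances, no dropout, and a paired effect held at 0.5 (raw shift 0.5·√(2(1 − r)) SD). The correlations are assumptions; the article gives none.

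| r | Mann-Whitney | Wilcoxon signed-rank | Paired t |
|---|---|---|---|
| 0 | 83.6% | 83.2% | 84.6% |
| 0.3 | 74.7% | 83.5% | 84.9% |
| 0.5 | 62.1% | 83.7% | 85.1% |
| 0.6 | 51.5% | 83.3% | 84.8% |
| 0.7 | 37.4% | 83.3% | 84.7% |

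A second run with 40,000 trials gave Mann-Whitney power of 84.0%, 74.1%, 61.7% and 38.0% at r = 0, 0.3, 0.5 and 0.7. The two runs agree to within about 0.6 points.

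**4. Where half the power is gone.** Half of 84.8% is 42.4%. Interpolating between r = 0.6 and 0.7 gives 0.6 + 0.1·(51.5 − 42.4)/(51.5 − 37.4) ≈ 0.66.

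**5. Sensitivity to the effect scale.** If 0.5 were a raw-SD effect, Mann-Whitney power at n = 30 would be 59%, 60%, 62%, 66% and 76% at r = 0, 0.3, 0.5, 0.7 and 0.9. The signed-rank test would have 58%, 71%, 83%, 96% and 100%. Mann-Whitney power then no longer falls as r rises, but its shortfall against the paired test remains for positive r.

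**The case against.** Several points in the plan's favour stand.

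- **The fallback is conditional.** It would only be considered, and only if assumptions are not clearly met. A reader might infer that the switch is likely because Likert-type scores and behaviour counts are often skewed. The article gives no distributional data, the t test's assumption concerns the paired differences rather than the raw scores, and at about 30 pairs that test is fairly robust.
- **The size of the loss is not known.** A reader might infer that most of the planned power would go. That holds only from a correlation of about 0.65–0.7 upward; at zero correlation the loss is negligible.
- **The simulated data are normal**, whereas the fallback is meant for data that are not. The figures show the mechanism; they do not estimate the loss in the situation that would trigger it.
- **The stakes are limited.** The stated aims are feasibility and fidelity. The Anticipated Findings section says a change could not be attributed to the intervention without a control group, and no progression rule rests on this p-value. With positive correlation the error does not favour a false claim of benefit.

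None of this makes Mann-Whitney suitable for paired data. It is the only alternative named, and responsive feeding is the declared primary outcome.

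**Conclusion.** The fallback is wrong as written: it is an independent-samples test for a study with no independent groups. Whenever pre and post scores are correlated, its p-values are miscalibrated. Under the normal-data assumptions above, the actual one-sided error is about 1.2% at a correlation of 0.5 and 0.2% at 0.7, and rises to about 6–7% at −0.2. Power at 30 dyads with a paired effect of 0.5 falls from about 84% at zero correlation to 62% at 0.5 and 37–38% at 0.7. The paired tests stay at about 83–85%.

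The direction for a given sign of correlation is firm. The magnitude is illustrative, because the correlation and the score distributions are not given. This should be fixed, but it does not undermine the planned analysis: the matched t test is appropriate, and 27 and 36 reproduce exactly.

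**What to change.** In Statistical Analyses, replace the Mann-Whitney U test with the Wilcoxon signed-rank test on the within-dyad differences (visit 5 minus visit 2). In the same sentence, state that the assumption checked is the distribution of those paired differences, not of the raw scores at each visit.

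The cost is one sentence. Data collection, sample size and budget are unaffected. In the simulation above, the signed-rank test keeps about 83–84% power at 30 dyads and an error rate close to 5% at every correlation examined.
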